## Abstract

**Background:**

Postprandial distress syndrome (PDS) has a considerable impact on quality of life. Our previous pilot trial suggested that acupuncture might be a potential treatment option for PDS. We will conduct this large trial to determine the efficacy of acupuncture versus sham acupuncture for PDS.

**Methods/design:**

A total of 280 eligible patients who meet the Rome IV criteria for PDS will be randomly allocated to either the acupuncture group or the sham acupuncture group. Each patient will receive 12 sessions over four weeks. The primary outcomes will be the response rate of overall treatment effect (OTE) and the elimination rate of all three cardinal symptoms (postprandial fullness, upper abdominal bloating, and early satiation) at four weeks after randomization. Secondary outcomes will include assessments of the severity of dyspepsia symptoms and disease-specific quality of life at weeks 4, 8, and 16 after randomization. All patients who receive randomization will be included in the intent-to-treat analysis.

**Discussion:**

The finding of this trial will provide high-quality evidence on the efficacy of acupuncture for treatment of PDS. Results of this research will be published in peer-reviewed journals.

**Trial registration:**

ISRCTN Registry, ISRCTN12511434. Registered on 31 March 2017.

**Electronic supplementary material:**

The online version of this article (10.1186/s13063-018-3051-3) contains supplementary material, which is available to authorized users.

## Background

Functional dyspepsia (FD) is a common functional gastrointestinal disorder [1]. In America, epidemiological surveys suggest that 12–15% of people have symptoms suggestive of FD [2]. About one-quarter of these people seek medical assistance [3]. Although FD is not a life-threatening disease [4, 5], quality of life (QoL) is considerably affected [6, 7]. The high rate of absenteeism and low productivity at work have substantial implications for patients, healthcare organizations, and society [8–10].

Trials testing treatment response by FD subgroup are urgently needed [11, 12]. Based on the Rome IV consensus, FD is subdivided into postprandial distress syndrome (PDS), characterized by postprandial fullness and early satiation, and epigastric pain syndrome (EPS), characterized by epigastric pain and burning [1]. There are different pathogenic mechanisms underlying these FD subgroups. PDS is associated with motility dysfunction and impaired gastric accommodation, while EPS is associated with a high prevalence of hypersensitivity to gastric distension [13]. PDS has a higher prevalence than EPS among the Asian population. Of 563 patients diagnosed with FD in Japan, 89% had PDS and 33% had epigastric pain syndrome, with an overlap in 22% [14]. It has been suggested that PDS patients may respond to a therapy that alters gastric motility [15], such as prokinetic drugs. However, these prokinetic drugs have been implicated in potential side effects, including parkinsonism syndrome and cardiac arrhythmia [16–18].

Acupuncture is widely accepted as an effective treatment option for gastrointestinal disorders in clinical practice [19]. A number of studies have shown that acupuncture is able to facilitate gastrointestinal motility [20, 21]. However, a recent meta-analysis of acupuncture for FD indicates that the efficacy of acupuncture for FD has not been verified because of poor quality of the trials [22]. To our knowledge, rare studies have been designed for PDS with acupuncture especially. A retrospective trial of FD shows that patients with PDS respond better to the acupuncture therapies than those with EPS [23]. The main objective of this trial is to evaluate the efficacy of acupuncture versus sham acupuncture for PDS.

## Methods

### Study design

This multi-center, randomized, participant-blind, sham-controlled trial will be conducted at five hospitals in China: Dongfang Hospital Affiliated to Beijing University of Chinese Medicine; Dongzhimen Hospital Affiliated to Beijing University of Chinese Medicine; Huguosi Hospital of Chinese Medicine Affiliated to Beijing University of Chinese Medicine; Beijing Hospital of Traditional Chinese Medicine Affiliated to Capital Medical University; and Beijing Friendship Hospital Affiliated to Capital Medical University. The study protocol has been approved by ethics committees at all participating hospitals, will follow the Declaration of Helsinki, and will be reported based on SPIRIT guidelines (Additional file 1) [24]. This trial has been registered with ISRCTN at Current Controlled Trials (ISRCTN12511434). A flow diagram of the trial is shown in Fig. 1.

**Fig. 1 Fig1:**
[figure not shown]
Flow diagram

### Patient recruitment

Patients meeting the Rome IV PDS criteria will be recruited primarily through advertisements on hospital social Internet media (WeChat) and newspaper, outpatient clinics, and publicity at community service centers. All patients will be required to provide written informed consent before randomization. Carbon-13 urea breath test will be routinely performed for patients due to the high prevalence of *H. pylori* infection in China.

#### Inclusion criteria

Aged 18–65 years (either sex);One or more of the following symptoms: postprandial fullness; upper abdominal bloating; or early satiation;Normal esophagogastroduodenoscopy results within one year;No acupuncture treatment in the last one month;No participation in any other research in the last two months.

#### Exclusion criteria

Dyspepsia symptoms caused by any serious or malignant disease, such as liver cirrhosis, heart failure, or gastrointestinal tumors;Surgery related to the gastrointestinal tract;Taking drugs which might affect dyspepsia, such as anti-secretary drugs, antacids, prokinetics, non-steroidal anti-inflammatory drugs, and antidepressant drugs within one month of participating in the trial;Difficulties in attending the trial, such as serious mental and physiological illness, dementia, or illiteracy;Severe coagulopathy;Drug or alcohol abuse;Pregnancy or breastfeeding.

### Randomization and allocation concealment

All eligible patients will be randomly assigned to the acupuncture group or sham acupuncture group in a 1:1 ratio with a central web-based randomization (Beijing Guide Technology Co., Ltd.). The blocked randomization sequence will be computer-generated with the SAS 9.3 software by a professional statistician, who is not involved in the implementation and statistical analysis of the trial. The clinical research coordinator will be responsible for enrolling patients, obtaining informed consent and requesting randomization.

### Masking

Due to the nature of acupuncture, masking of acupuncturists is quite difficult to achieve. Patients, outcome assessors, and statisticians who perform the statistical analyses will be blinded to group assignment. Participant’s allocated intervention will be not revealed until the statistical analysis is completed.

### Interventions

Treatment will be performed by licensed acupuncturists who have at least three years of experience in acupuncture. All the acupuncturists will be trained how to locate acupoints and non-acupoints, puncture, and manipulate needles before the trials. Sterile disposable acupuncture needles (length: 25–40 mm, diameter: 0.25 mm; Hwatuo, Suzhou, China) will be used. Both the acupuncture and sham acupuncture treatments will consist of 12 sessions with 20-min duration over four weeks (three sessions per week, ideally every other day). Acupuncture will be discontinued if the patients suffer from any adverse events (AEs). Other treatments which may affect the dyspepsia symptoms will be prohibited, such as antacids, prokinetics, non-steroidal anti-inflammatory drugs, antidepressant drugs, and so forth.

#### Acupuncture

Patients allocated to the acupuncture group will take treatment with needles inserted at the prespecified acupuncture points. The protocol including obligatory and additional acupoints was developed from the clinical experience of acupuncture experts. The obligatory acupoints included *Baihui (DU20)*, *Danzhong (RN17)*, *Zhongwan (RN12)*, and *Qihai (RN6)*, and bilateral *Tianshu (ST25)*, *Neiguan (PC6)*, *Zusanli (ST36)*, and *Gongsun (SP4)*. According to different Traditional Chinese Medicine syndromes, additional acupoints could be chosen individually: *Taibai (SP3)* for weakness of the *qi* of the spleen and stomach; *Taichong (LR3)* for depression of the *qi* of the liver; and *Neiting (ST44)* for damp-heat in the stomach. All acupoints are localized according to the WHO Standard Acupuncture Locations and exhibited in Table 1 and Fig. 2. Manipulations of twirling, lifting, and thrusting will be performed on all needles for at least 30 s to reach *De qi* (a compositional sensation including soreness, numbness, distention, and heaviness), which is believed to be an essential component for acupuncture efficacy.

**Table 1 Tab1:** Locations of acupoints in acupuncture group

Acupoints	Locations
Baihui (*DU20*)	On the midline of the head, 7 cun^a^ directly above the midpoint of the posterior hairline
Danzhong (*RN17*)	On the anterior midline, on the level of the 4th intercostal space, at the midpoint of the line joining the two nipples
Zhongwan (*RN12*)	On the anterior midline, 4 cun above the umbilicus
Tianshu (*ST25*)	On the same level of the umbilicus, and 2 cun lateral to the anterior midline
Qihai (*RN6*)	On the anterior midline, 1.5 cun below the umbilicus
Neiguan (*PC6*)	On the line joining Daling (*PC7*) and Quze (*PC3*), between the tendons of palmaris longus and flexor carpi radialis, 2 cun above the transverse crease of the wrist
Zusanli (*ST36*)	3 cun directly below Dubi (*ST35*), and one finger-breadth lateral to the anterior border of the tibia
Gongsun (*SP4*)	On the medial aspect of the foot, anteroinferior to the base of the first metatarsal bone, at the border between the red and white flesh
Taibai (*SP3*)	On the medial aspect of the foot, in the depression proximal to the first metatarsophalangeal joint, at the border between the red and white flesh
Taichong (*LR3*)	In the depression anterior to the junction of first and second metatarsal bones
Neiting (*ST44*)	On the dorsum of the foot, between the second and third toes, posterior to the web margin, at the border between the red and white flesh

^a^1 cun (≈20 mm) is defined as the width of the interphalangeal joint of patient’s thumb

**Fig. 2 Fig2:**
[figure not shown]
Locations of acupoints and non-acupoints

#### Sham acupuncture

A superficial skin penetration (2–3 mm in depth) at non-acupoints will be performed in the sham acupuncture group, without needle manipulation for *De qi*. Non-acupoints are away from conventional acupoints or meridians and are shown in Table 2 and Fig. 2.

**Table 2 Tab2:** Locations of non-acupoints in sham acupuncture group

Non-acupoints	Locations
Non-acupoint 1	In the middle of Touwei (*ST8*) and Yuyao (*EX-HN4*) points
Non-acupoint 2	2 cun^a^ above the anterior superior iliac spine
Non-acupoint 3	2 cun below the umbilicus, and 1.0 cun lateral to the anterior midline. cun below the umbilicus, and 1 cun lateral to the anterior midline
Non-acupoint 4	In the middle of the medial epicondyle of the humerus and the styloid process of ulna
Non-acupoint 5	3 cun below Yanglingquan (*GB34*), between the gallbladder and bladder meridian
Non-acupoint 6	In the middle of Qiuxu (*GB40*) and Jiexi (*ST41*) points

^a^1 cun (≈20 mm) is defined as the width of the interphalangeal joint of patient’s thumb

Although it is difficult to set an eligible placebo control, superficial insertion at non-acupoints is the most commonly used approach for administering sham treatments among acupuncture trials on the basis of a literature review [25]. And this study will exclude those received acupuncture treatment in the last one month. This population can most probably distinguish sham acupuncture from acupuncture. The same control, shallow needling at non-acupoints, was adopted and is successful to mask Chinese participants with chronic severe functional constipation [20]. Furthermore, all participants will be asked to guess which treatment they have received to test the patient-blinding effects.

### Outcomes

#### Primary outcomes

The two primary outcomes are the response rate based on overall treatment effect (OTE) and the elimination rate of all three cardinal symptoms: postprandial fullness; upper abdominal bloating; and early satiation (no symptoms) at the end of treatment (four weeks after randomization) [26].

When assessing OTE, outcome assessors will evaluate patients using a 7-point Likert scale. The question is “How were your gastric symptoms during the past week in comparison with the baseline period?”, which closely resembles the way physicians evaluate treatment benefit in clinical practice. The answers will include “extremely improved,” “improved,” “slightly improved,” “not changed,” “slightly aggravated,” “aggravated,” and “extremely aggravated” [26]. Patients who answer “extremely improved” or “improved” will be considered as responders. Although there is no universally accepted primary outcome established for therapeutic trials in FD, OTE is a frequently used outcome [27], which has been used as the primary outcome in several trials [28–30].

The elimination rate of three cardinal symptoms was added as another primary outcome. Because the U.S. Food and Drug Administration has argued against the use of OTE as a single primary outcome for its recall bias. After trial commencement, the Data and Safety Monitoring Board (DSMB) suggested that we could use combined primary outcomes for our study. Similarly, the pattern of two primary outcomes was adopted in a study evaluating acotiamide in FD [26]. The elimination rate is based on the severity of dyspepsia symptoms [31] and is defined as the proportion of patients whose scores of postprandial fullness, upper abdominal bloating, and early satiation all decline to 0 [26].

Acupuncture will be considered as an effective therapy, only if both primary outcomes achieve significant difference to avoid type I error accumulation. All protocol amendments are described in detail in Additional file 2.

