## Severity of dyspepsia symptoms

The severity of eight dyspepsia symptoms, including postprandial fullness, early satiation, upper abdominal bloating, epigastric pain, epigastric burning, nausea, vomit, and belching, will be assessed at baseline, once every week in treatment period and at weeks 8, 12, and 16. The severity of each symptom is scored as asymptomatic (0 point), mild (1 point), moderate (2 points), or severe (3 points) [31].

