### Statistical methods

#### Sample size

Since acupuncture is a complex intervention, it is different from drugs. The efficacy of acupuncture will be altered, if the acupoints in the study are changed. For this reason, literature data speculation is not adopted in this trial. Based on previous clinical experience, the proportions of acupuncture and sham acupuncture responders for OTE are expected to be 55% and 35%, respectively. For elimination of all the three symptoms, the proportions are expected to be 26% and 10%, respectively. A two-sided significance level is 0.05. A sample size of 224 (112 patients in each group) was estimated to have at least 80% power to detect significant differences. The power was calculated as the product of the power of each endpoint: 82.5% and 84.3%. To compensate for a 20% attrition rate, the sample size expands to 140 patients in each group.

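### The elimination co-primary is worded as a fall to 0 on all three symptoms, although patients may enter without all three; it should be a state at week 4, compared with adjustment for baseline score

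*Protocol article*

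**What the plan says.** Four statements in the Protocol article bear on this.

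- *Inclusion criteria*: a patient qualifies with "One or more of the following symptoms: postprandial fullness; upper abdominal bloating; or early satiation". All three are not required.
- *Severity of dyspepsia symptoms*: "The severity of each symptom is scored as asymptomatic (0 point), mild (1 point), moderate (2 points), or severe (3 points". An absent symptom therefore has a baseline score of 0.
- *Primary outcomes*, opening sentence: the outcome is elimination of the three cardinal symptoms, ending with "early satiation (no symptoms) at the end of treatment (four weeks after randomization". This describes a state at a fixed time.
- *Primary outcomes*, later definition: elimination "is defined as the proportion of patients whose scores of postprandial fullness, upper abdominal bloating, and early satiation all decline to 0". This describes a change from baseline.

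Under *Sample size*, "For elimination of all the three symptoms, the proportions are expected to be 26% and 10%, respectively", with 112 evaluable patients per arm and 84.3% power for this endpoint. Under *Statistical analysis*, categorical variables are compared by Fisher's exact test or the Wilcoxon rank-sum test, and no baseline covariate is named.

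**The concern.** The sentence that formally defines the endpoint does not fit the eligibility rule. A programmer working from it would require each of the three scores to drop. A patient who enters without bloating, for example, would be a failure however well the other symptoms resolve. The opening sentence of the same section would make that patient a success. Nothing in the article says how a baseline 0 is counted.

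The numerator matters because acupuncture is to be called effective only if both primary outcomes are significant. This endpoint was also added after the trial had started, so its definition should be beyond doubt before allocation is revealed. The same rule is used again at weeks 8, 12 and 16.

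A related, smaller point concerns efficiency. Even with the state rule, the distance to success differs between patients. One mild symptom needs a change of 1 point; three severe symptoms need 3 × 3 = 9 points. The named tests make no use of this baseline information.

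**Working it through.** **Step 1: the two wordings applied to one patient.** Take an eligible patient who scores fullness 2, bloating 0 and early satiation 1 at baseline, and 0, 0, 0 at week 4 (an illustration on the article's 0–3 scale).

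| Wording | Bloating item (0 to 0) | Classification |
|---|---|---|
| All three scores decline to 0 | Did not decline | Non-responder |
| No symptoms at end of treatment | Symptom absent | Responder |

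The two agree for patients with all three symptoms at baseline. They can differ for everyone else.

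**Step 2: reproduce the stated power.** Inputs from *Sample size*: p1 = 0.26, p2 = 0.10, n = 112 per arm, two-sided 0.05. The normal approximation with pooled null variance and continuity correction is

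power = Φ{[(p1 − p2) − 1/n − 1.96·SE0] / SE1}, where SE0 = √[2p̄(1 − p̄)/n], SE1 = √{[p1(1 − p1) + p2(1 − p2)]/n} and p̄ = (p1 + p2)/2.

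- p̄ = 0.18; SE0 = √(0.2952/112) = 0.0513; SE1 = √(0.2824/112) = 0.0502.
- (0.16 − 0.0089 − 0.1006)/0.0502 ≈ 1.00, so power = 84.2% (stated: 84.3%).
- The same formula gives 82.5% for the overall treatment effect outcome (55% versus 35%; stated: 82.5%), so this appears to be the method used.

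**Step 3: state reading.** A baseline 0 that stays at 0 counts as clear. With the planned rates taken as trial-wide rates, nothing changes: 84.2%.

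**Step 4: literal reading.** Let s be the share of patients with all three symptoms at baseline. The article does not give s, so it is an assumption. If 26% and 10% are the rates among those patients, the trial-wide rates become 0.26s and 0.10s. For s = 0.8:

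- p1 = 0.208, p2 = 0.080, p̄ = 0.144; SE0 = √(0.2465/112) = 0.0469; SE1 = √(0.2383/112) = 0.0461.
- (0.128 − 0.0089 − 0.0920)/0.0461 ≈ 0.59, so power = 72.2%.

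| s (assumed) | Rates | Power, formula above | Power, exact Fisher |
|---|---|---|---|
| 100% | 26.0% v 10.0% | 84.2% | 85.6% |
| 90% | 23.4% v 9.0% | 78.8% | 80.3% |
| 80% | 20.8% v 8.0% | 72.2% | 73.5% |
| 60% | 15.6% v 6.0% | 55.6% | 56.2% |

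These are powers for the elimination endpoint alone, at 112 per arm.

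**The case against.** The strongest reply is that there is only one sensible rule. The opening sentence of *Primary outcomes* describes a state at four weeks, and the symptom scale defines 0 as asymptomatic. Together these mean that all three scores are 0 at week 4, and *decline* is loose wording. I accept that this is the likelier intent.

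A reader might go further and infer that the trial excludes patients with a baseline 0 from ever responding, or that it is underpowered for that reason. The article does not support either inference. It nowhere says that such patients are to be counted as failures. The power loss needs the literal reading, a share with all three symptoms that is not reported, and planned rates that apply only to that subgroup. *Sample size* does not tie the rates to a subgroup. If they already allow for baseline zeros under whichever rule was meant, they should not be scaled down. The scaling also ignores that patients with fewer or milder symptoms may clear more easily.

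Nor can it be claimed that entry has no severity floor. Under *Patient recruitment*, "Patients meeting the Rome IV PDS criteria will be recruited primarily", and the content of those criteria is not reproduced. The listed inclusion criteria set no minimum score on the 0–3 scale, and that is all that can be said.

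On adjustment, randomization makes the unadjusted test valid, and an analysis plan that is not shown may add covariates. The article also gives no evidence on how strongly baseline score predicts elimination. The proposal is therefore an improvement in efficiency and does not correct an invalid test.

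What remains is that the protocol itself states the definition, and followed as written it would misclassify eligible patients. That is not a detail left to another document.

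**Conclusion.** The point holds as a defect of definition. The formal wording of a co-primary endpoint conflicts with the eligibility rule and with the outcome description in the same section. For any patient with a baseline 0 who is clear on all three symptoms at week 4, the classification depends on which sentence is followed.

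Its size depends on the reading. On the likelier state reading there is no loss. On the literal reading, power for this endpoint would be about 79%, 72% or 56% with 90%, 80% or 60% of patients having all three symptoms, subject to the assumptions in Step 4. These figures show why the wording should be settled; they do not forecast this trial's power. Baseline adjustment is a secondary recommendation, and its gain cannot be quantified from the article.

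**What to change.** Before unblinding:

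1. In *Primary outcomes*, replace the change wording with: *all three scores (postprandial fullness, upper abdominal bloating, early satiation) equal 0 at week 4, whatever the baseline value*. Apply it to all randomized patients with no baseline restriction, so that the intent-to-treat set is unchanged. A patient with a symptom at week 4 that was absent at baseline is then clearly a non-responder. Use the same rule at weeks 8, 12 and 16.
2. In *Statistical analysis*, compare elimination between arms with adjustment for the baseline sum (0–9) of the three scores, for example by logistic regression, instead of relying only on the unadjusted test. State in advance which of the two analyses decides the endpoint.

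The cost is one rewritten sentence and one covariate in the model. The three scores are already recorded at baseline, so no new data and no change to the sample size are needed.

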#### Secondary outcomes

OTE at other time points

Response rate according to OTE and the elimination rate of all three cardinal symptoms will also be measured at weeks 8, 12, and 16 after randomization.

